#### Termination criteria

(1) Serious adverse events (life-threatening or affecting normal general work and life) occur; (2) in the course of treatment, the symptoms disappear completely and the patients are unwilling to receive treatment again; and (3) patients with severe and persistent anaphylaxis will stop treatment and be treated as invalid cases.

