## Method/design

### Study design

According to the random number table method [13], a total of 60 patients with DLI will be divided into sitting lumbar rotation manipulation group (the intervention group) and supine lumbar traction group (the control group), 30 cases in each group. DLI patients will be numbered according to the visit time, and any one number in the random number table will be selected as the starting point. A random number corresponding to each patient will be obtained along the same direction. Divide this number by 2, and the remainder of 0 will be the intervention group, and the remainder of 1 will be the control group. Two residents participating in this study will be responsible for generating the allocation order sequence.

The treatment of the two groups lasted for 3 weeks. The manipulation of the intervention group would be carried out once every other day, three times a week, a total of 9 times; the control group would be given lumbar traction once a day, five times a week, a total of 15 times. JOA [14] and VAS [15] scores will be recorded as the primary outcomes before the treatment and at the 1st, 3rd, 5th, 8th, 10th, 12th, 15th, 17th, and 19th days after the first treatment and follow-up visit at the 1st, 3rd, and 6th months. JOA [14] efficacy evaluation standard will be used to evaluate the overall efficacy as the secondary outcomes. When analyzing the results, the personnel who collect the data are blind to the grouping situation. The flow of this clinical trial is shown in Fig. 1; the schedule of enrolment, assessments, and interventions is presented in Table 1. JOA [14] and VAS [15] scores are presented in Table 2 and Fig. 2.

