### Randomization, allocation concealment, and blinding

Upon completion of the baseline assessment, participants were randomly assigned by the physician to the sitting lumbar rotation manipulation group and the supine lumbar traction control group. Because doctors and patients are able to know which kind of intervention will be accepted, they cannot be blind to the treatment, but the result evaluator and data statistician are blind to the grouping and treatment.

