#### Lumbar traction in supine position control group

The operation of the lumbar traction in supine position [21] treatment method is as follows: the patient is in supine position with the chest band fixed in both armpits and the pelvic band fixed in the upper edge of the iliac crest. The tightness of binding is moderate. The traction weight starts from a small amount and increases to 50% of the patient’s weight. During traction, a triangular brace is placed in the lumbosacral part of the patient, which is located at the lower edge of the lumbar sliding instability segment. It will be taken once a day, 5 times a week, 30 min each time.

Implementing seated lumbar rotation manipulation and lumbar traction in the supine position group will not require alteration to usual care pathways (including use of any medication) and these will continue for both trial arms.

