### Safety measurements

During the intervention period, researchers will monitor the occurrence of adverse events; observe the type, degree, and incidence of adverse events; and record and handle them. If there are any adverse events, such as trauma, the adverse event case report form (CRF) will be used for detailed reporting. In addition, the researchers will specifically note the causal relationship and severity of adverse events in the evaluation of seated lumbar rotation manipulation intervention. If serious adverse events occur, they will be reported to the ethics committee.

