### Data collection and management

The outcome assessors will use the CRF papers to collect the data. The CRF papers will be randomly put into envelopes of different groups and sent to a researcher who is responsible for electronic data input. Then, the researcher will transcribe the CRF into an electronic data acquisition system (EDC), which is a free Research Manager named ResMan (http://www.medresman.org) provided by the China Clinical Trial Registry and meets the available standards for security. Every subject will be assigned a separate experiment identification number, and the relevant data will be strictly confidential. Only members of the trial will have access to the data set. Anonymized trial data will be shared with other researchers to enable international prospective meta-analyses. The research data will be stored in the EDC system in a separate password-protected location. Data Monitoring Committee was not considered as this is a low-risk intervention.

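### Causal relationship to treatment is specified only for adverse events in the manipulation arm, so treatment-related harms could not be compared fairly with traction

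*Protocol article*

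**What the plan says.** Two sections of the protocol article bear on this.

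**Safety measurements.** Adverse events are monitored during the intervention period. Researchers will "observe the type, degree, and incidence of adverse events", and will record and handle the events. Any event goes on an adverse event case report form. For serious events the text says: "If serious adverse events occur, they will be reported to the ethics committee". None of these steps names an arm. One further sentence does: researchers will "specifically note the causal relationship and severity of adverse events in the evaluation of seated lumbar rotation manipulation intervention". It is the only mention of causality in the article, and nothing equivalent is said of traction.

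**Termination criteria.** The first criterion reads "Serious adverse events (life-threatening or affecting normal general work and life) occur". The words in brackets are the article's only definition of a serious adverse event.

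For context, the control is also a physical treatment of an unstable spine: "The traction weight starts from a small amount and increases to 50" per cent of body weight. On blinding, the article says of doctors and patients that "they cannot be blind to the treatment, but the result evaluator and data statistician are blind to the grouping and treatment".

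**The concern.** The trial compares two active physical treatments, either of which could cause harm. A fair comparison of treatment-related events needs the same question asked, in the same way, of every event in each arm. If staff follow the sentence as written, an event after manipulation receives a judgement on whether the treatment caused it, and the same event after traction need not. An excess of related events after manipulation could then reflect closer scrutiny, and a harm caused by traction could go unattributed.

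The definition of a serious event raises a smaller matter. Meeting it is a criterion for termination and triggers a report to the ethics committee, yet its second limb sets no boundary of degree or duration. In this disease the boundary matters, because restricted activity is part of the condition: 14 of the 29 points of the JOA scale (Table 2) measure it.

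**Working it through.** The plan states no figure on this point and no arithmetic applies. The check sets the statements side by side.

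**Step 1. What is stated for whom (Safety measurements).**

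| Item | Manipulation | Traction |
|---|---|---|
| Occurrence monitored in the intervention period | yes | yes |
| Type, degree, incidence | yes | yes |
| Adverse event form | yes | yes |
| Serious events reported to the ethics committee | yes | yes |
| Causal relationship | yes | not stated |
| Specific note on severity | yes | not stated, but degree is recorded |

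Degree is in effect severity, so the last row is largely covered by the second. The firm difference is the causality row.

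**Step 2. Follow one event through.** Take the same event, say new leg pain after a session, in one patient per arm. Both events are observed, graded, entered on the form and counted in all-cause incidence. Both meet or fail the same definition of serious. Only the event after manipulation has a stated judgement of cause. A table of all adverse events by arm is therefore like for like. A table of treatment-related events is not, because the traction column has no stated procedure behind it.

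**Step 3. Who makes the judgement.** On the plain reading, a note made for one treatment only requires knowledge of the allocation. The blinding section lists the result evaluator and the statistician as blind; it does not say that whoever judges causality is. The article also states that a "Data Monitoring Committee was not considered as this is a low-risk intervention". That is a reasoned choice and not the fault here, but it means no such committee would see the imbalance.

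**Step 4. The definition of serious.** The first limb, threat to life, is a degree. The second, interference with work and daily life, has none. Short-lived soreness that limits lifting for a day could be classed as serious by one reader and minor by another. The definition applies equally to both arms, so it creates uncertainty in classification and no built-in difference between arms.

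**The case against.** The strongest reply is that the causality sentence is loosely worded and means the whole trial. It does not say that only manipulation events are assessed. The Abstract and the Introduction both describe the two-arm trial as a study of the effect of the manipulation, so evaluating the manipulation could simply mean conducting this trial. That reading is possible. It is not the plain one, since the sentence names one intervention and staff will work from the words. If the whole trial was meant, a few words settle it.

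A second reply is that a condensed article leaves form fields and formal definitions to the full protocol. That stands as far as missing detail goes: the form cannot be seen, and its fields may already be identical for both arms. The point, however, rests on a sentence the article does contain, not on one it omits.

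A third is that treatment-related events are named in no outcome or planned analysis, so little depends on them. This limits the consequence. It does not remove it, because a causality judgement made for one arm invites a comparison that it cannot support.

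A reader might also infer more than the text supports:

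- **That harms in general are assessed differently in the two arms.** The first four rows of the table show otherwise.
- **That serious-event rates would be biased.** The serious label has the same definition in both arms and does not depend on the causality note.
- **That the definition of serious lacks any degree.** Only its second limb does.
- **That the problem can be sized from the planned numbers of sessions, or from the weight of one event in an arm of 30.** The first describes exposure and the second holds for any arm of that size; neither measures bias.

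**Conclusion.** The concern holds in a narrow form. As written, causal attribution, with an extra note on severity, is specified for one of two active treatments, and treatment-related events could not be compared fairly between the arms. The extent is one assessment item in the safety comparison. All-cause adverse event counts, serious-event reporting, JOA and VAS are unaffected. No numerical size can be given, because the article states no adverse event rate and none is assumed here.

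The conclusion rests on the plain reading of one sentence. If the sponsor confirms that both groups were meant, what remains is a correction of wording. The open-ended second limb of the definition of serious is a separate and minor point. This is a cheap improvement worth making, not a defect in the design.

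**What to change.** 1. **Safety measurements (the main change).** Reword the causality sentence so that causal relationship to the allocated treatment and severity are recorded for every adverse event in both groups, by the same procedure and in the same fields of the existing adverse event form.
2. **Definition for ethics reporting (minor).** Use the standard outcome-based definition of a serious adverse event: death, threat to life, new or prolonged hospitalisation, significant or persistent incapacity, or another medically important event.
3. **Termination criteria (minor).** Keep the present low threshold for stopping treatment, written as its own rule: stop for a serious adverse event, or for any adverse event that interferes with normal work or daily life. Stopping then no longer depends on the serious label, and no protection is lost.

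The cost is new wording in two sections and slightly more form-filling for traction patients. No extra visits, patients or staff are needed.

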### Recruitment

Participants will be recruited by the spine doctors of Wangjing Hospital of the Chinese Academy of Traditional Chinese Medicine through posters, design of network recruitment, and sending flyers. According to the inclusion and exclusion criteria mentioned above, 2 chief physicians in this clinical trial will select appropriate patients to join the study.

There will be trained staff to discuss the informed consent with the enrolled patients.

After obtaining consent and signing informed consent form, baseline assessment shall be conducted.

### Randomization, allocation concealment, and blinding

Upon completion of the baseline assessment, participants were randomly assigned by the physician to the sitting lumbar rotation manipulation group and the supine lumbar traction control group. Because doctors and patients are able to know which kind of intervention will be accepted, they cannot be blind to the treatment, but the result evaluator and data statistician are blind to the grouping and treatment.

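### The allocation concealment section describes no step that keeps the next assignment from the staff who enrol or treat, so as written the arm can be known before a patient is accepted

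*Protocol article*

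**What the plan says.** The procedure is spread over three sections of the protocol article.

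- **Study design.** The order of patients is set by attendance: "DLI patients will be numbered according to the visit time". A starting point in a random number table is picked, and from there "A random number corresponding to each patient will be obtained along the same direction". The arm follows from parity: "Divide this number by 2, and the remainder of 0 will be the intervention group, and the remainder of 1 will be the control group". On who does this: "Two residents participating in this study will be responsible for generating the allocation order sequence".
- **Recruitment.** Spine doctors at the hospital recruit, and "2 chief physicians in this clinical trial will select appropriate patients to join the study". Trained staff discuss consent, and the baseline assessment follows the signed consent form.
- **Randomization, allocation concealment, and blinding.** Once baseline is complete, "participants were randomly assigned by the physician to the sitting lumbar rotation manipulation group and the supine lumbar traction control group". Of doctors and patients it says "they cannot be blind to the treatment, but the result evaluator and data statistician are blind to the grouping and treatment".

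That last section gives no means of holding or releasing the sequence. The only envelopes in the article are in Data collection and management, where they carry completed case report forms to data entry.

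**The concern.** Randomization protects a comparison only if those who decide whether a patient enters cannot foresee the arm. Here the sequence comes from study staff, patients are ordered by when they attend, trial physicians judge suitability, and an unblinded physician assigns. No barrier between the sequence and these people is described.

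Someone who knows the next arm can hasten, delay or decline a patient, or change the order in which two patients are taken. The arms may then differ in prognosis from the start. Treatment is unblinded, VAS is self-rated, and much of the JOA score is symptoms and restriction in activities, so a difference in expected course between the arms could pass for a treatment effect. Blinding the evaluator and the statistician guards against biased assessment and analysis. It has no bearing on who was enrolled into which arm.

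**Working it through.** No figure in the plan is in dispute here, so the check sets the stated steps side by side and asks, at each one, what is fixed and who could know it.

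1. **Is the sequence determined in advance?** Yes. Under Study design there are three inputs: the starting point, the direction of reading and the parity rule. Once the first two are chosen, patient 1, patient 2 and so on each have a fixed arm.
2. **Is a patient's place in the sequence known early?** Numbering follows visit time. The article does not say whether the number is given at presentation or only after enrolment. On the first reading it is fixed before selection and consent. On the second, the next unused number is still known to anyone who knows how many have been enrolled.
3. **Who can see the sequence?** The two residents, because they generate it. They are described as participating in the study, and nothing excludes them from recruiting, treating or assessing. The physician who assigns must learn at least the current entry, and nothing limits that physician to one entry at a time.
4. **Who decides on entry?** The two chief physicians. Nothing says whether either of them is also the assigning physician, or that they are kept from the sequence.
5. **Is there a concealment step?** None is described in the section named for it, or elsewhere in the article.
6. **What does the stated order add?** The order is selection, consent, baseline, then assignment. This prevents the assignment from formally preceding consent. It does not prevent someone from consulting a sequence that already exists.

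**Predictability of the next arm**

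- With access to the sequence: probability 1.0, since the table and the patient number fix the arm.
- Without access: probability 0.5, since each entry is even or odd with equal chance and earlier entries carry no information.

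The 0.5 takes the parity rule as the only rule. Any extra step used to reach the stated 30 per group would be a separate matter, and the article does not describe one.

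**Can analysis repair it?** Baseline JOA and VAS are recorded before assignment, so an imbalance in them can be seen and at least partly adjusted for. A clinician's impression of who will do well is not recorded, and selection on it cannot be adjusted away.

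**The case against.** The strongest case on the other side has four parts.

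- **Access is not stated.** A reader might infer that the list lies open to the doctors, or that the assigning physician holds it. No section says so. Different roles are named for generating, selecting, obtaining consent and assigning, and they may be different people. This stands: the article supports only the statement that no concealment is described.
- **The article is condensed.** A full protocol (version 1.0, according to Trial status) is not shown, and it may describe envelopes or a central service. This stands in part. However, the article gives the method down to the remainder after division, and has a section on concealment whose text states assignment by the physician. That is a stated procedure with a gap at its key point, which goes beyond ordinary abbreviation.
- **Assignment already follows consent and baseline.** This is true and should be kept. It answers when assignment takes place, not who could know it beforehand.
- **Predictability to the holder is a property of any list made in advance.** Also true, including of a well-concealed one. The 1.0 therefore measures what access would give, not how likely access is. This is why the holding and release of the list have to be specified.

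Two further inferences are not supported. That doctors know the treatment once it is given is not foreknowledge of allocation. And nothing in the article shows that enrolment was steered, or by how much the result would move if it were.

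**Conclusion.** The point holds in a limited form. As written, the procedure allows the next arm to be known before a patient is accepted, because a fully determined sequence is generated by study staff and no step keeps it from those who enrol or treat. The conclusion rests on the article's own description and assumes that no concealment measure is set out in the full protocol. If one is, the remaining task is to state it in the section that bears its name.

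The size that can be given is predictability: 1.0 with access, 0.5 without, for each of the 60 planned allocations. The documents give no basis for a figure for bias in JOA or VAS, so none is offered. Imbalance in measured baseline scores could be partly corrected in analysis; selection on unmeasured prognosis could not. That makes this a safeguard to specify at small cost, not evidence that the allocation has been compromised.

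**What to change.** For further enrolment:

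- The two residents may go on generating the list, but take no part in recruiting, treating or assessing.
- The list is held in sequentially numbered, opaque, sealed envelopes or in a central web allocation system.
- Each assignment is released singly, and only after eligibility, consent and baseline JOA and VAS have been irrevocably recorded. This keeps the existing order and makes it enforceable.
- The section on allocation concealment states these steps and says who holds the list.

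For patients already enrolled (Trial status gives 1 May 2020 as the start of recruitment), the sponsor should document who held the sequence, who had access to it and when, and give this in the trial report.

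The cost is a set of envelopes or the set-up of a web allocation, plus a small logistic burden at each enrolment. Sample size, interventions and outcomes are unchanged.

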### Intervention

#### Seated lumbar rotation manipulation group

The seated/sitting lumbar rotation manipulation [20] treatment in this group will be divided into three parts, which are examination, preparation and treatment technique. It will be carried out once every other day, three times a week, a total of 9 times.
Examination technique

Patients stand straight, feet apart and shoulder width, hands naturally droop, exposing the waist and back. The doctor observed whether there was physiological curvature of the spine, whether there was scoliosis, and then palpated with index finger, middle finger, and ring finger. Doctors use the middle finger to move from top to bottom along the apex of the spinous process. The index finger and ring finger are on both sides of the middle finger. They can feel whether there is any abnormality in the arrangement of spinous processes, whether there is a deviation of spinous processes to one side, whether the adjacent spinous processes are not in a straight line, or step sense. Make the patient lumbar flexion and extension, and then carry out the above examination. Doctors combined with imaging examination and physical examination to determine the abnormal stage of lumbar spine and the oblique position of spinous process.
b.Preparation technique

The patient is in a prone position and relaxed. The doctor’s hands are placed on both sides of the patient’s spine, on the surface of the sacrospinalis muscle, from the outside to the inside, from the shallow to the deep, pushing and rubbing the vertical spine muscle rhythmically, and shaking the lumbar spine left and right at the same time. The function of this method is to relax muscles, relieve muscle spasm, release adhesion, activate blood circulation and remove blood stasis, dredge channels and collaterals, and relieve spasm and pain. Take the next step when your muscles are relaxed.
iii.Treatment technique

The doctor will use the controllable treatment chair (Fig. 3) for manual treatment. According to the height and weight of the patient and the height of the doctor, the height and distance of the patient chair and the doctor chair are adjusted by using the calculation results of the parameter formula. The patient sits on this special treatment chair, relaxes the waist with both legs fixed. The doctor puts one hand against the spinous process of the unstable segment of the lumbar spine, and the other hand passes through the armpit of one side of the patient, pressing the neck and shoulder of the other side. First, let the patient slowly bend the spine forward. When the doctor’s thumb feels the interspace of spinous process open, maintain this range. Then let the patient rotate to this side as much as possible. Finally, the doctor flexes and rotates the patient’s lumbar vertebrae with the hand pressed on the neck and shoulder. The thumb of the other hand pushes the spinous process of the abnormal vertebral body. At this time, it can often be heard the “click” sound, and the doctor can feel the spike jump under the thumb holding the spike. Repeat the same maneuver on the opposite side. The treatment technique can be simply summarized into three parts: flexion, rotation, and pulling, as shown in Fig. 4.

